### Outcomes

The primary outcome is to compare the rate of diagnostic accuracy of EUS-FNB using the two different suction techniques (dry suction and wet suction). The rate will be calculated as the sum of true positive values and true negative values divided by the total number of samples, with an accurate diagnosis defined as a final diagnosis consistent with the tissue sample obtained during the needle passes.

The secondary outcomes include the optimal number of needle passes, sensitivity, specificity, specimen quality, cytological diagnoses, time of the procedure, and incidence of complications. Specificity analysis is only applicable to participants without malignancy, whereas sensitivity analysis is only applicable to persons with malignancy.

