### Final diagnosis

The malignant diagnosis was defined as the cytological or pathological diagnosis considered suspicious or positive for malignancy. Neuroendocrine tumors, solid pseudopapillary neoplasm, lymphoma, and melanoma were also considered to be malignant lesions.

The final diagnostic standards are as follows:For patients who undergo surgery, the final diagnosis will be based on the definite evidence of malignancy from surgical specimens.For patients who did not receive surgery, the final diagnosis will be considered as malignancy if cytologic or histologic diagnosis of malignancy is made by EUS-FNB with a corresponding clinical manifestation.For patients with negative or unsatisfactory pathological results, the final diagnosis will be confirmed by clinical and imaging follow-up for 1 year. If there was no imaging progression of the SPL, the true negative would be considered, and if there was progression or death, the false negative would be determined.

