### Sample size calculation

The sample size calculation was based on the primary outcome of diagnostic accuracy for the evaluation of solid pancreatic lesions. The reported diagnostic accuracy of EUS-FNB for SPL using dry suction is approximately 96.2%, and the wet suction technique is about 98.3% in the literature [6, 8]. Based on the reported data and the clinical judgment, the non-inferiority of dry suction in EUS-FNB will be assessed with a non-inferiority (*δ*) margin of 10%. With a two-sided test, a significance level of 2.5% (*α* = 0.025), and a power (1 − *β*) of 90%, using the PASS 15.0 software and a sample allocation ratio of 1:1 between the dry suction and wet suction groups, 180 patients should be enrolled. Considering a 10% dropout rate, a final sample of 200 participants (100 per group) is needed.

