Second, surgical pathological data was not available in all patients with SPLs. Some patients do not undergo surgery because the lesion is benign or because they refuse surgical treatment. Thus, clinical and imaging follow-up will be done for at least 12 months to determine the final diagnosis.

In conclusion, this is the first multicenter randomized controlled trial designed to clarify whether the dry suction technique is non-inferior to the wet suction technique and the optimal needle passes for SPLs using a 22G Franseen needle. The findings may provide high-level evidence of EUS-FNB procedures in clinical practice.

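### For unoperated patients with a negative or unsatisfactory biopsy, any death in follow-up counts as a false negative whatever its cause, which conflicts with the plan's own true-negative rule

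*Protocol article*

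**What the plan says.** The Final diagnosis section of the protocol article sets the reference standard by route.

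- Operated patients: "For patients who undergo surgery, the final diagnosis will be based on the definite evidence of malignancy from surgical specimens".
- Negative or unsatisfactory biopsy: "For patients with negative or unsatisfactory pathological results, the final diagnosis will be confirmed by clinical and imaging follow-up for 1 year".
- Rule within that follow-up route for calling the biopsy right: "If there was no imaging progression of the SPL, the true negative would be considered".
- Rule within the same route for calling it wrong: "if there was progression or death, the false negative would be determined".

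The Discussion repeats that, because not all patients have surgical pathology, "clinical and imaging follow-up will be done for at least 12 months to determine the final diagnosis".

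The Outcomes section carries these labels into the primary endpoint: "The rate will be calculated as the sum of true positive values and true negative values divided by the total number of samples". It also restricts sensitivity to patients with malignancy.

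**The concern.** Death and progression are alternatives in the false-negative clause, so death suffices by itself. The clause asks for no cause, no attribution to the pancreatic lesion and no review, and there is no category for a patient whose status cannot be established. Eligibility runs to age 85 and follow-up lasts a year, so some deaths from other causes are plausible.

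Take a patient with a benign lesion, a correct negative biopsy and stable imaging who then dies of an unrelated cause. The true-negative clause scores the biopsy right and the false-negative clause scores it wrong. Two centres could score the same patient differently, each following the text.

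If the false-negative clause prevails, the patient leaves the numerator of the primary outcome and enters the sensitivity denominator without having been shown to have malignancy. Few failures are planned, so each one weighs on the non-inferiority comparison.

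**Working it through.** **1. The plan's own figure.** From the Sample size calculation section: "The reported diagnostic accuracy of EUS-FNB for SPL using dry suction is approximately 96.2" per cent for dry suction; "the wet suction technique is about 98.3% in the literature" for wet; margin 10 points; alpha 0.025; power 90%; 1:1 allocation.

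n per arm = (1.960 + 1.282)² × (0.962×0.038 + 0.983×0.017) / (0.10 − 0.021)² = 10.51 × 0.05327 / 0.006241 = 89.7, so 90 per arm and 180 in all; 180 / 0.9 = 200. The plan's figures reproduce with alpha taken as one-sided 0.025. Power at 90 per arm is 90.1%.

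**2. Planned failures.** Dry: 90 × 0.038 = 3.4. Wet: 90 × 0.017 = 1.5. One relabelled patient moves an arm's accuracy by 1/90 = 1.1 points.

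**3. How many patients the rule could mislabel.** The article gives no inputs for this, so these are assumptions: k = 10 to 30 negative or unsatisfactory unoperated patients overall, and unrelated one-year mortality q = 3 to 10%.

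- Expected number = k × q: 10 × 0.03 = 0.3, up to 30 × 0.10 = 3.
- Chance of at least one = 1 − (1 − q)^k: 1 − 0.97^10 = 26%, up to 1 − 0.90^30 = 96%.

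**4. Effect when the arms are affected equally.** An assumed middle case: 15% of each arm in this group and 5% unrelated mortality. The share mislabelled is 0.15 × 0.05 = 0.0075, or 0.7 patients per arm of 90. Accuracies become 97.55% (wet) and 95.45% (dry). The true difference is unchanged, but the variance grows and power falls from 90% to 82%.

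**5. Effect when one arm is affected.** If dry accuracy alone is lower by 1/90, power is about 72%. If wet alone is lower by 1/90, power rises to about 92%.

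**6. How close results lie to the margin.** The interval is my choice: Wald 95%, lower limit = (d − w) − 1.96 × √[d(1−d)/90 + w(1−w)/90]. With wet at 88/90:

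| Dry | Lower limit (points) |
|---|---|
| 87/90 | −5.9 |
| 86/90 | −7.5 |
| 85/90 | −9.0 |
| 84/90 | −10.4 |

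The step from 85 to 84 crosses the margin: −0.0333 − 1.96 × 0.0287 = −0.090, then −0.0444 − 1.96 × 0.0305 = −0.104. A Newcombe interval crosses one patient earlier (86/90 gives −8.9, 85/90 gives −10.3).

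Summing the binomial probabilities of all outcomes at the planning rates, about 13% of the probability lies on results that are non-inferior by Wald but would not be with one more dry failure.

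**The case against.** **The rule does not mislabel every death.** A reader might infer that it does, but operated patients have the surgical specimen as reference standard, and a death from a missed pancreatic cancer is rightly a false negative. An unsatisfactory sample is not a correct benign result, so counting it as inaccurate after a death is arguably no error. All of this stands. It also means that the 0.3 to 3 in step 3, which applies mortality to the whole group, leans high.

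**No bias between arms is shown.** The rule is the same in both randomised arms, and nothing in the article suggests that unrelated deaths depend on suction technique. This stands. Balance holds only in expectation, though: with so few events a split of one to none is ordinary, and equal mislabelling still costs power.

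**The 85 to 84 step is a boundary case.** It means 5 against 2 failures, not the planned 3.4 against 1.5. From 87/90 against 88/90, three extra failures, all in the dry arm, are needed to cross. This stands. Nor is the 26 to 96% a chance of a changed conclusion: it counts a death in either arm. The 13% is also only one factor, since a spurious failure must then occur and fall in the dry arm.

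**The article is condensed.** The reference to clinical follow-up leaves some room for judgement, and the full protocol may define attribution of death; that cannot be checked here. But the article does not merely omit a detail. It states two rules that give opposite answers for the same patient.

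**Conclusion.** The point holds for unoperated patients with a negative or unsatisfactory biopsy. As written, death alone makes a false negative, and this contradicts the preceding true-negative clause for anyone who dies with a stable lesion. The patient clearly mislabelled is the one with a correct benign biopsy who dies of an unrelated cause.

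The size rests on assumptions about the number of negatives and unrelated mortality. It is probably 0 to 3 patients overall, expected to be similar in the arms. The expected consequence is lower measured accuracy and sensitivity and some loss of power, to about 82% in the assumed middle case. A reader might go further and conclude that the rule tilts the comparison or usually decides it; the documents support neither. The contradiction in the text does not depend on any of these assumptions. It is worth correcting because it affects the primary endpoint and costs little to mend.

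**What to change.** Reconcile the two clauses in the Final diagnosis section:

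- After a negative biopsy, score a false negative only when progression or death is attributable to pancreatic malignancy on imaging, tissue or recorded cause of death.
- Have this judged without knowledge of the arm. The Randomization and blinding section states blinding only for cytologists and pathologists.
- Classify other deaths after a negative biopsy on the evidence available up to death. Where there is none, record the reference standard as unverified.
- Report the non-inferiority result with the unverified patients counted both ways.

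The cost is a short change of wording, one cause-of-death field on the follow-up form, one sensitivity analysis, and a few patients left with an unverified reference standard. Trial status reports 123 patients enrolled by October 2023, with recruitment expected to run to June 2024, so cause of death can still be collected for much of the cohort. The rule should be settled before outcomes are seen by arm.

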### Data collection and management

The data will be collected using case record forms (CRF) by trained doctors. Figure 2 shows the schedule of enrollment, interventions, and assessments. We will conduct regular quality checks and validation procedures and implement strict protocols for data security and storage to ensure data quality, security, and storage.

Our study team will make maximum effort to have participants complete the study follow-up assessments. The study team will contact participants via telephone to collect as much outcome data as possible. All data obtained until the time of withdrawal will be retained in the study.

A comprehensive data management plan is implemented to ensure data quality, security, and storage. This includes using standardized CRF templates and guidelines for data entry, conducting regular quality checks and validation procedures, and implementing strict protocols for data security and storage.

Biological specimens will be collected during the surgical procedures and used for routine diagnostic tests. The biopsy samples will be stored in the Pathology Department of the hospital. No genomic or molecular analysis are planned in the current trial or for future use.

### Confidentiality

Only the informed consent forms will contain patient names and will be stored locally in a safe location at each participating center. Personal data about participants is retained using an identifier in the CRF. Only the authorized research team will be granted access to personal information about participants.

### Sample size calculation

The sample size calculation was based on the primary outcome of diagnostic accuracy for the evaluation of solid pancreatic lesions. The reported diagnostic accuracy of EUS-FNB for SPL using dry suction is approximately 96.2%, and the wet suction technique is about 98.3% in the literature [6, 8]. Based on the reported data and the clinical judgment, the non-inferiority of dry suction in EUS-FNB will be assessed with a non-inferiority (*δ*) margin of 10%. With a two-sided test, a significance level of 2.5% (*α* = 0.025), and a power (1 − *β*) of 90%, using the PASS 15.0 software and a sample allocation ratio of 1:1 between the dry suction and wet suction groups, 180 patients should be enrolled. Considering a 10% dropout rate, a final sample of 200 participants (100 per group) is needed.

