### Statistical analysis plan

The full analysis set should be as close as possible to the intention-to-treat set. The direct deletion method will be used to treat missing data.

Continuous variables will be summarized as means with standard deviation and compared with *t*-tests or Wilcoxon rank-sum tests. Categorical variables will be expressed as percentages using the *χ*^2^ test or the Fisher exact test. Differences in diagnostic yield between the two techniques will be evaluated with the chi-squared test. Statistical significance will be considered for *P* < 0.05. All statistical analyses will be performed using SPSS (version 25.0, IBM, Armonk, NY).

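### The sample size statement says a two-sided 2.5% test, but its 180 patients and 90% power match a one-sided 2.5% test; as written the power is about 84%

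*Protocol article*

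**What the plan says.** The section Sample size calculation gives a complete set of inputs:

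- Accuracy "using dry suction is approximately 96.2"% and "the wet suction technique is about 98.3"%.
- An absolute non-inferiority margin of 10%.
- "With a two-sided test, a significance level of 2.5"% (α = 0.025).
- Power "of 90%, using the PASS 15.0 software", and "a sample allocation ratio of 1:1 between the dry suction and wet suction groups".
- The result: "180 patients should be enrolled", raised to 200 (100 per group) for 10% dropout.

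The section Statistical analysis plan gives one threshold for all tests: "Statistical significance will be considered for" P < 0.05. It does not say whether this is one- or two-sided, and it sets no separate level for the non-inferiority test. Nowhere does the article describe the 2.5% as one-sided or tie the primary conclusion to a 95% confidence interval.

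**The concern.** For a non-inferiority comparison, a one-sided 2.5% test and a two-sided 5% test are the same criterion: the relevant limit of a two-sided 95% interval is compared with the margin. A two-sided test at 2.5% is neither of these. It puts 1.25% in the non-inferiority tail and corresponds to a 97.5% interval.

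The level fixes the decision rule for the primary conclusion. An analyst who follows the sample size section literally would apply the stricter limit, with too few patients for the stated power. One who follows the analysis section could use a 95% interval or, taking P < 0.05 as one-sided, a 90% interval. If this is settled only after the results are known, the choice can be challenged as post hoc.

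**Working it through.** **Inputs** (all from Sample size calculation): dry suction (test) 0.962; wet suction (control) 0.983; margin 0.10; power 0.90; 1:1 allocation; α = 0.025; dropout 10%.

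**Formula** (two proportions, non-inferiority, unpooled normal approximation):

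n per arm = (z₁₋ₐ + z₀.₉₀)² × [p_dry(1 − p_dry) + p_wet(1 − p_wet)] / [margin − (p_wet − p_dry)]², where a is the probability in the non-inferiority tail.

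- Variance term: 0.962 × 0.038 + 0.983 × 0.017 = 0.036556 + 0.016711 = 0.053267.
- Distance to the margin: 0.10 − 0.021 = 0.079; squared, 0.006241.

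**Step 1: reproduce the plan's figure (one-sided 2.5%).** (1.960 + 1.282)² × 0.053267 / 0.006241 = 89.7, so 90 per arm and 180 in total; 180 / 0.9 = 200. Both stated figures are reproduced exactly.

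**Step 2: the level as printed (two-sided 2.5%, a = 0.0125).** (2.241 + 1.282)² × 0.053267 / 0.006241 = 105.9, so 106 per arm and 212 in total; 212 / 0.9 = 235.6, so 236.

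**Step 3: power at the planned size.** Power = Φ(0.079 / SE − z₁₋ₐ), with SE = √(0.053267 / n).

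| Level | Total evaluable needed for 90% | Power, 90 per arm | Power, 100 per arm |
|---|---|---|---|
| One-sided 2.5% | 180 | 90.1% | 92.8% |
| Two-sided 2.5% (as printed) | 212 | 84.3% | 88.1% |
| One-sided 5% | 148 | 94.5% | 96.2% |

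**Step 4: sensitivity to the formula.** At the two stated rates, the two-sided 2.5% reading gives 212 (unpooled), 214 (pooled), 262 (continuity-corrected) or 342 (Farrington-Manning). None is 180. One-sided 2.5% gives 180 with the unpooled formula, and also with the formula that pools the variance under the null.

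**Step 5: can the conclusion change?** A constructed example, with Wald intervals and 90 evaluable per arm: 85/90 accurate with dry suction and 89/90 with wet.

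- Difference: 0.9444 − 0.9889 = −4.44 points.
- SE = √(0.9444 × 0.0556 / 90 + 0.9889 × 0.0111 / 90) = 2.655 points.
- Lower limit, 95% interval: −4.44 − 1.960 × 2.655 = −9.65 points. Non-inferiority is shown.
- Lower limit, 97.5% interval: −4.44 − 2.241 × 2.655 = −10.40 points. Non-inferiority is not shown.

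**The case against.** The strongest reply is that the design is sound and only the word for the side is wrong. The numbers 180 and 200 come out exactly under the usual convention, and P < 0.05, read as two-sided, is that same convention. The analysis section would then help to settle the matter rather than add a conflict. A literal reading would also be conservative: it costs power and does not raise the false-positive risk.

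Much of this stands. The calculation is very probably right and its description wrong. But the reader has to infer this: P < 0.05 carries no side, and on any reading it disagrees with the printed two-sided 2.5%. Nor is this detail that an article may leave to a fuller document, because the article itself states two thresholds that do not agree.

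Three technical limits also stand:

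- **The match depends on the formula.** The article names the software but not the test. Farrington-Manning needs 284 in total at one-sided 2.5% and 342 at two-sided 2.5%, so neither reading gives 180 under that test.
- **One other route comes close.** With both arms set to 96.2%, two-sided 2.5% gives 182. That discards the stated 98.3% and still misses 180.
- **The powers are approximations.** At 90 per arm only about 3.4 (90 × 0.038) and 1.5 (90 × 0.017) inaccurate diagnoses are expected. Exact enumeration of the Wald test gives about 86% at one-sided 2.5% and 81% at 1.25%. The fall of about five to six points remains, but neither 90% nor 84% is exact.

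**Conclusion.** The concern holds. On the article's own inputs and the standard normal formula, 180 patients with 90% power correspond to a one-sided 2.5% level. The printed two-sided 2.5% level would require 212 evaluable patients (32 more) and 236 enrolled (36 more). At the planned 180 it gives 84.3% power; with no dropout at all it gives 88.1%, still short of 90%.

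These figures assume the stated rates of 96.2% and 98.3%, the 10-point margin and the normal approximation. The contradiction does not depend on which approximation is used, since no formula tried turns the printed level and the two stated rates into 180. The remedy is small, but the fault lies in the error rate of the primary conclusion and must be corrected before the final analysis.

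**What to change.** In Sample size calculation, replace the description of the level with: *one-sided significance level of 2.5%, equivalent to using a two-sided 95% confidence interval*. Name the test or formula used in the software, so that 180 can be reproduced.

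In Statistical analysis plan, state the same rule for the primary outcome: dry suction is non-inferior if the lower limit of the two-sided 95% confidence interval for the difference in accuracy (dry minus wet) lies above −10 percentage points. Keep two-sided P < 0.05 for the secondary comparisons only.

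The cost is wording, recorded as a dated protocol clarification; 180 and 200 stand. The Trial status section reports 123 patients enrolled by 13 October 2023 and recruitment expected to finish by June 2024, so on that timetable the clarification could precede the final analysis. If the sponsor does mean a two-sided 2.5% level, wording is not enough: the target becomes 212 evaluable and 236 enrolled, or the stated power must be lowered to about 84%.

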## Background

Endoscopic ultrasound-guided fine-needle aspiration/biopsy (EUS-FNA/B) is an efficient diagnostic technique for solid pancreatic lesions (SPLs). Compared with FNA needles, the FNB needles can obtain much more core tissue, making histological investigations and genetic testing widely used, contributing to precision medication.

A novel wet suction technique for EUS-FNA was developed to improve the quality of aspirates and reduce blood contamination for diagnosis performance [1]. For the “wet suction” technique, the needle was flushed with saline solution to replace the column of air and then aspiration with a-10 ml pre-vacuum syringe. This is based on the principle that water is a less compressible fluid compared to air. Therefore, the volume of the vacuum could be enhanced when the EUS needle is filled with water (wet technique) [2]. A recent, randomized trial by Yun W. et al. has demonstrated that EUS-FNA using the wet technique is superior to the standard method in terms of diagnostic accuracy, sample adequacy, and sample blood contamination [3]. However, there are few studies on the impact of wet aspiration on the diagnostic accuracy of EUS-FNB. The sample size of these studies is small, and the conclusions are controversial.

The 2017 European Society for Gastrointestinal Endoscopy (ESGE) guidelines suggest the performance of two to three passes with an FNB needle when on-site cytologic evaluation is unavailable [4]. An RCT study demonstrated that the diagnostic accuracy of EUS-FNB alone with 3 needle passes in patients with SPLs reached 97.4% [5]. Of note, a recent large-scale multicenter RCT study showed that the overall diagnostic accuracy of FNB for SPLs was 94.7%, with an average of 2.81 passes required [6]. Unlike the reverse bevel needle, a needle with Franseen geometry was used in this study, and a meta-analysis showed that the Franseen needle was significantly superior to the reverse-bevel needles in both diagnostic accuracy and sample adequacy [7]. Further research is needed to explore the optimal needle passes of EUS-FNB using the Franseen needle.

The purpose of this multicenter RCT study is to compare the diagnostic accuracy of the dry suction technique versus the wet suction technique in SPLs using a 22G Franseen needle and determine the optimal passes required for EUS-FNB. This study may provide high-level evidence of EUS-FNB procedures for clinical practice.

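### The 180 patients for 90% power rest on a normal approximation that is poor at 96–98% accuracy; at the planning rates a method that holds about 2.5% has roughly 73% power

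*Protocol article*

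**What the plan says.** The protocol article's Sample size calculation gives the planning rates: "The reported diagnostic accuracy of EUS-FNB for SPL using dry suction is approximately 96.2" per cent, and "the wet suction technique is about 98.3% in the literature". It sets a non-inferiority margin of 10%. The error is introduced with "With a two-sided test, a significance level of 2.5" per cent (alpha = 0.025), and the size follows from a power "of 90%, using the PASS 15.0 software and a sample allocation ratio of 1:1 between the dry suction and wet suction groups, 180 patients". Allowance for loss is then added: "Considering a 10% dropout rate, a final sample of 200 participants (100 per group) is needed".

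The section does not say which test statistic or variance formula was chosen in the software. The Statistical analysis plan section names a test for one comparison, "Differences in diagnostic yield between the two techniques will be evaluated with the chi-squared test", with significance at P < 0.05. It names no non-inferiority statistic or interval.

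**The concern.** Both planning rates lie close to 100%, so the power calculation turns on a handful of inaccurate diagnoses per arm. That is where a simple Z statistic for a difference in proportions behaves badly. Its standard error is estimated from very few failures and is often too small, so the test declares non-inferiority too readily.

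If 180 came from such a formula, the stated 90% and 2.5% are nominal values, not properties the trial has at its own assumptions. Non-inferiority on accuracy is the primary aim. At stake is either a chance of missing it that is well above the planned 10%, or a non-inferiority claim with more false-positive risk than stated.

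**Working it through.** **Inputs** (all from Sample size calculation): dry p_D = 0.962; wet p_W = 0.983; margin 0.10, read as an absolute difference; alpha 0.025, used one-sided; power 0.90; allocation 1:1; dropout 10%.

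**1. Reproduce 180.** Unpooled normal approximation:

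n per arm = (z_0.975 + z_0.90)² × [p_D(1 − p_D) + p_W(1 − p_W)] / (0.10 − (p_W − p_D))²

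- Variance term: 0.962 × 0.038 + 0.983 × 0.017 = 0.036556 + 0.016711 = 0.053267
- Distance to the margin: 0.10 − 0.021 = 0.079; squared, 0.006241
- (1.960 + 1.2816)² = 10.507
- n = 10.507 × 0.053267 / 0.006241 = 89.7, so 90 per arm and 180 in total
- 180 / 0.9 = 200

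The formula's own power at 90 per arm is 90.1%. A pooled-variance Z also gives 90 per arm. Other choices do not give 180:

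| Variant | n per arm |
|---|---|
| Continuity-corrected Z | 114 |
| Farrington-Manning score, asymptotic power | 142 |
| Z at one-sided 0.0125 (two-sided 2.5% read literally) | 106 |
| Z at one-sided 0.05 | 74 |

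**2. Expected failures.** Inaccurate diagnoses per 90 patients: dry 90 × 0.038 = 3.4; wet 90 × 0.017 = 1.5.

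**3. Exact operating characteristics.** All outcomes of the two binomials were enumerated, and non-inferiority was declared when the statistic reached 1.96. Power is at 96.2% v 98.3%. Type I error is on the margin, where dry equals wet minus 10 points.

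| Method | n per arm | Power | Type I error at 88.3% v 98.3% | Maximum type I error, wet 90–100% |
|---|---|---|---|---|
| Wald (unpooled Z) | 90 | 85.9% | 4.6% | 5.1% |
| Farrington-Manning score | 90 | 73.3% | 2.2% | 2.5% |
| Wald (unpooled Z) | 100 | 87.2% | 3.8% | 5.8% |
| Farrington-Manning score | 100 | 77.0% | 2.1% | 2.5% |

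At the two points in the power and 88.3% v 98.3% columns, the Newcombe 95% interval gives the same figures as the score test at both sample sizes. Pooled Z gives the same figures as Wald.

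**4. Where the gap comes from.** Take 5 inaccurate diagnoses in 90 (dry) and 1 in 90 (wet). The distance from the margin is 0.10 − 4/90 = 0.0556.

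- Wald standard error: √[((5/90)(85/90) + (1/90)(89/90)) / 90] = 0.0266, so Z = 2.09 and non-inferiority is declared.
- Score: the rates fitted under a 10-point difference are 0.893 and 0.993, giving a standard error of 0.0338, Z = 1.64 and no declaration.

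Outcomes like this are common at the planning rates, so a small shift in the decision boundary moves power by about 13 points (85.9% − 73.3%).

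**5. Other true rates.** Score power at 90 per arm with equal accuracy in both arms is 86% at 96.2%, 91% at 97% and 97% at 98.3%.

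**The case against.** **It is not a slip of arithmetic.** This stands. The software output is correct for the formula used; the fault lies in applying that formula at these rates. The formula is also inferred: the normal approximation is well supported, but unpooled and pooled forms cannot be told apart.

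**The analysis method may sit in a statistical analysis plan that is not shown.** This stands in part. Nothing says the primary test will be Wald, so a reader who infers that the trial will run at a 4.6% error goes beyond the documents. That figure describes what follows if the analysis matches the calculation. The power statement is different: it is in the protocol, and none of the methods checked makes it true together with the stated alpha at the planning rates.

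**The planning rates are cautious.** They build in a 2.1-point deficit for dry suction, while the Discussion expects the two techniques to be equally good. A reader might conclude that 90 per arm can never give both 90% and 2.5%. That is too strong: with equal accuracy of about 97% or higher, score power exceeds 90%. The shortfall belongs to the rates the protocol chose for its calculation.

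**A worse scenario is tempting.** The Background reports that "the overall diagnostic accuracy of FNB for SPLs was 94.7%, with an average of 2.81 passes required [6"], and that reference is one of two cited for the planning rates. Taking 94.7% as the dry rate would give 65% power by the normal formula and 48% by the score test. The documents do not support this: 94.7% is an overall FNB figure, is not attributed to dry suction, and the text does not say which source supplied 96.2%.

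**Score and Newcombe methods are not exact.** This is correct. Over the whole boundary at 90 per arm their type I error reaches 2.7% and 3.1%, at wet accuracies of about 55–65%, far from this setting. An exact unconditional score test held to 2.5% everywhere has 66.6% power, so 73% is not a pessimistic choice.

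**Conclusion.** The point holds. The protocol's 180 patients are right for a normal approximation, but the power attached to them is not. At 96.2% v 98.3% with 90 evaluable per arm, power is about 73% for a score or Newcombe method that holds about 2.5% for wet accuracy of 90–100%. The chance of missing non-inferiority is then about 27%, where 10% was planned. Full retention of 200 patients raises power only to 77%. A Wald analysis would have about 86% power, still below 90%, with an error of about 4.6%.

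For scale, 90% score power at these rates would take roughly 135–140 evaluable patients per arm.

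The conclusion assumes the protocol's own rates, an absolute margin of 10 points and one-sided alpha of 0.025. The last is the kinder reading of the alpha sentence: taken literally as two-sided 2.5%, score power at 90 per arm is about 55%.

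**What to change.** 1. Use a score-type interval (Farrington-Manning or Miettinen-Nurminen) or a Newcombe interval for the primary non-inferiority comparison. If the statistical analysis plan already names one, only the next item is needed.

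2. Restate the power in Sample size calculation, for example: with 90 evaluable patients per arm, power is about 73% (about 77% with 100) at true accuracies of 96.2% (dry) and 98.3% (wet), margin 10 percentage points, one-sided alpha 0.025, by the score method.

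3. If a sensitivity line is wanted, show a range of true rates that includes equal accuracy in both arms (score power at 90 per arm about 86% at 96.2% and 91% at 97%). Do not present 94.7% as the dry-suction rate.

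The cost is a less favourable stated power and some wording. No patients are added. Trial status reports 123 patients enrolled by October 2023, and the change can be made at any time before the primary analysis.
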